## Abstract

**Background:**

The nationwide integration of palliative care best practices into general care settings is challenging but important in improving the quality of palliative care. This is why the Dutch National Quality Improvement Programme for Palliative Care has recently been launched. This four-year programme consists of about 70 implementation trajectories of best practices. A large evaluation study has been set up to evaluate this national programme and separate implementation trajectories.

**Methods/Design:**

This paper presents the protocol of the evaluation study consisting of a quantitative effect evaluation and a qualitative process evaluation. The effect evaluation has a pre-test post-test design, with measurements before implementation (month 0) and after implementation (month 9) of a best practice. Patients are eligible if they have a life expectancy of less than six months and/or if they are undergoing palliative treatment and provided they are physically and mentally capable of responding to questionnaires. Bereaved relatives are eligible if they have been involved in the care of a deceased patient who died after a sickbed between six weeks and six months ago. Three types of measurement instruments are used: (1) numerical rating scales for six symptoms (pain, fatigue, breathlessness, obstipation, sadness and anxiety), (2) the Consumer Quality Index Palliative Care - patient version and (3) the version for bereaved relatives.

The process evaluation consists of analysing implementation plans and reports of the implementation, and individual and group interviews with healthcare professionals. This will be done nine to eleven months after the start of the implementation of a best practice.

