### National quality improvement programme for palliative care

The Dutch National Quality Improvement Programme for Palliative Care was launched in 2012 with the aim of promoting the implementation of best practices in general health care settings. This four-year programme receives financial and practical support from ZonMw (The Netherlands Organisation for Health Research and Development) and was commissioned by the Dutch Ministry of Health. The programme’s key objectives are to promote that:

•Patients die at their preferred place.

•Patients and relatives feel they are in control regarding palliative care.

•Patients and relatives see palliative care as being coordinated.

•Patients and relatives feel care to be concordant with their needs, preferences and values.

•Patients and relatives receive care for their needs in the physical, psychosocial and spiritual domains.

This programme enables care organizations to improve their palliative care by implementing one or more of the available best practices. The best practices are pre-selected by an independent committee of experts, professionals and patient representatives, taking account of the available evidence, the usability and the transferability of the best practice to general health care settings. The committee assesses potential new best practices every year to include in the National Quality Improvement Program Palliative Care. The nine best practices that are currently pre-selected for implementation are listed in Additional file 1.

Every year during the programme period (2012–2016), there is a call for applications. Representatives of regional networks of palliative care providers are invited to choose a specific best practice from the pre-selected list and to submit a project proposal for an implementation trajectory. Each year, financial support is given by ZonMw for approximately 17 implementation trajectories. The grant applications are assessed by an independent quality working group. The criteria for granting this support include the requirement that the applicant must be a representative of the regional palliative care networks, the care organizations involved must reach a substantial number of patients with palliative care needs and the best practice chosen must be implemented within one year [10].

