### Effect evaluation

Pre-test and post-test measurements will take place in the effect evaluation, in month 0 and month 9 respectively (see Figure 2). During these two measurement months, eligible patients and bereaved relatives will be asked to participate.

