### Process evaluation

A qualitative process evaluation will be conducted nine to eleven months after the start of the implementation in a separate implementation trajectory (see Figure 2). The process evaluation will be used to explain the effects found (or not found) in the effect evaluation and provide insight into how the best practices are implemented.

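### The relatives' month-9 post-test covers deaths in about months 3.0 to 7.6, while implementation may take a year, so it is not assured to measure care after implementation

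*Protocol article*

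**What the plan says.** The Abstract (Methods/Design) calls the two assessments "measurements before implementation (month 0) and after implementation (month 9) of a best practice". The Effect evaluation section repeats months 0 and 9 and adds: "During these two measurement months, eligible patients and bereaved relatives will be asked to participate". Relatives are eligible if they were "involved in the care of a deceased patient who died after a sickbed between six weeks and six months ago".

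On the pace of implementation, the Background section on the national programme gives a grant condition: "the best practice chosen must be implemented within one year". The Process evaluation section places the qualitative work "nine to eleven months after the start of the implementation in a separate implementation trajectory". Together with a month 0 that lies before implementation, this supports counting month 9 from the start of implementation rather than from its completion.

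The Data analysis section under Effect evaluation compares pre-test with post-test in a multilevel model. It names levels for care networks or organisations and for type of best practice, and no term for exposure or date of death. In Table 2, place of death appears only among the relatives' indicators.

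**The concern.** Patients report on current care at month 9. Relatives look back, and the admissible deaths all occurred at least six weeks earlier. The two groups therefore describe different exposure periods under one post-test label. For relatives, that label holds only if the best practice was already in use when the patient was being cared for.

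The mismatch is one-sided. Relatives assessed at month 0 describe care given wholly before implementation. Relatives assessed at month 9 may describe care given while implementation was still under way. Analysing all of them as post-test dilutes whatever the programme achieved.

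Relatives are about two thirds of planned respondents. Research question 1a, on dying in the preferred place, rests on them alone. A weak or null result there could be read as a programme without effect when it partly reflects timing. The Discussion lists feedback reports, respondent burden and scattered patients as difficulties, but not this lag.

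**Working it through.** **The plan's own numbers.** The Study population section gives 17 trajectories a year, two assessments, four years, and minimum targets of 15 patients and 30 relatives per assessment.
- Patients: 17 × 15 × 2 = 510 a year; × 4 = 2040.
- Relatives: 17 × 30 × 2 = 1020 a year; × 4 = 4080.

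Both stated totals reproduce. Relatives' share: 4080 / (2040 + 4080) = 67%.

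**Death window.** Six weeks is 42 / 30.44 = 1.38 months.
- Assessed at month 9.0: from 9 − 6 = 3.0 to 9 − 1.38 = 7.6.
- Assessed at month 10.0, the end of a measurement month: from 4.0 to 8.6.
- Overall span if recruitment runs through the month: 3.0 to 8.6.

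Every admissible death precedes month 9. One relatives' indicator concerns the patient's last month of life, so the care described reaches back to about month 2 for the earliest deaths. The month-0 assessment covers deaths from 6 to 1.4 months before month 0, all before implementation.

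**Illustration A, step change.** Assumptions: deaths are spread evenly over months 3.0 to 7.62 (width 4.62), and the practice has no effect before month g and full effect from g. Share of post-test deaths before g = (g − 3) / 4.62, limited to 0–100%.

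| g | Share of deaths before g |
|---|---|
| 3 | 0% |
| 4 | 1 / 4.62 = 22% |
| 6 | 3 / 4.62 = 65% |
| 7.6 or later | 100% |

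**Illustration B, gradual uptake.** Assumptions: the same spread of deaths, and effect proportional to uptake, which rises linearly from month 0 to completion at month T. Retained share = mean of min(t/T, 1) over the window.

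| T | Calculation | Retained |
|---|---|---|
| 6 | (3 / 4.62) × 0.75 + (1.62 / 4.62) × 1 | 84% |
| 9 | mean death time 5.31 / 9 | 59% |
| 12 | 5.31 / 12 | 44% |

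If every relative were assessed at month 10.0, the retained shares would be 93%, 70% and 53%. If uptake is complete by month 3, nothing is lost.

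**When the whole window would clear.** The earliest death lies six months back, so the assessment could not start before T + 6: month 12, 15 or 18 for T = 6, 9 or 12.

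**The case against.** The strongest reply is that the deciding input is not given. No date is stated for when any best practice came into use. One year is a funding ceiling, not a schedule, and a trajectory finished by month 3 is unaffected. Figure 2 and the additional files with the full eligibility criteria are not reproduced in the text at hand. This stands: neither the existence nor the size of dilution in a given trajectory can be shown. It does not make the label secure, because a trajectory that uses the time it is allowed will have post-test deaths before the practice is fully in place.

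A reader might infer three stronger things that the documents do not support:
- **That these deaths were unexposed or came before implementation.** On the article's clock, every post-test death falls at least three months after the start. These are deaths during implementation, and for a complex intervention some effect before completion is plausible.
- **That the estimated effect is biased towards zero.** Only the programme's component is diluted. The design has no control group, and secular trend or the feedback reports could move the observed difference either way.
- **That the whole primary objective fails.** Questions 1b to 1d also have patient-reported indicators, which lack the bereavement look-back, although a month-9 assessment can also precede completion at month 12.

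The process evaluation asks whether implementation went as planned and is meant to help explain effects found or not found. That makes an unexamined null conclusion less likely. It does not change which deaths the relatives' estimate contains.

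**Conclusion.** The concern holds in a limited form. The article's own figures place relatives' post-test deaths at about months 3.0 to 7.6, at most 8.6, against an implementation period of up to twelve months. The description of month 9 as after implementation is therefore not assured for relatives. Nothing in the text gives them a later assessment or sorts them by date of death.

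Where the practice came into use after about month 3, the programme's part of the relatives' pre-post difference is diluted, and question 1a has no other source. The amount is unknown. The illustrations run from no loss to complete loss under a step change, and from 84% to 44% retained under linear uptake completed between months 6 and 12. They rest on evenly spread deaths, on month 0 being the start of implementation, and on the assumed shape of uptake. They show sensitivity to timing and are not estimates of bias.

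**What to change.** 1. Reconcile the timing statements in the Abstract, the Background section on the national programme, the Effect evaluation section and the Process evaluation section. State from which event month 9 is counted, and acknowledge the look-back for relatives.
2. For each organisation, record the date the best practice came into use, from the implementation plans and reports already collected. For each relative's response, record date of death or time since death, which eligibility already requires.
3. Pre-specify an exposure analysis for relatives' outcomes: death before or after that date, or time since that date, as a term in the multilevel model. Report it beside the all-respondents result.
4. State in advance that a null relatives' result will not be read as no programme effect where most deaths precede the date of use.

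The cost is one extra date per organisation and some analysis text. The exposed group will be smaller and its intervals wider. With a step change at month 6, about 35% of 30–40 relatives, or roughly 11–14 per trajectory, would be exposed. For late-implementing trajectories the group may be empty, which is why the all-respondents result should stay alongside.

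A later posting to relatives is optional. Clearing the whole window needs the date of use plus six months, which may not fit the annual cycle.

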**Discussion:**

This mixed-method evaluation study gives more insight into the effects of the total programme and the separate implementation trajectories. However, evaluation of large quality improvement programmes is complicated due to changing, non-controlled environments. Therefore, it is important that an effect evaluation is combined with a process evaluation.

**Trial registration:**

NTR-4085

## Background

Death comes to us all. Nowadays, acute deaths due to infectious diseases have largely been replaced by non-sudden deaths, caused by e.g. cancer, cardiovascular diseases and dementia [1]. Therefore, the need for palliative care is increasing. High-quality palliative care is important in improving the quality of life of patients and their families facing the problems associated with a life-threatening disease [2]. Since the 1990s, the Dutch government has consistently invested in the optimization of palliative care, and nowadays many best practices are available in the Netherlands. 'Best practices' are defined in this paper as practices, often developed among small groups of patients and professionals, that contribute to the improvement of palliative care and that are transferrable to other settings. Some examples of best practices in the Netherlands are:

The Dutch version of the Liverpool Care Pathway for the Dying Patient [3]. The pathway was developed to aid members of a multi-disciplinary team in matters relating to continuing or discontinuation of treatments and regarding comfort measures during the last days and hours of a patient's life.

PaTz – a systematic approach to optimize palliative care based on the Gold Standard Framework (http://www.goldstandardsframework.org.uk/). Its elements include collaborative meetings of general practitioners and community nurses, the timely identification of patients in need of palliative care and the drafting of an advance care plan [4].

Informare, a tailored method that enables health care professionals to provide timely information about palliative care to patients and relatives [4].

‘Signal box for nursing assistants’, a tool that enables nursing assistants to identify palliative care needs in their patients and pass this information on to other professionals [4].

These best practices are known for their contribution to high-quality palliative care, although so far most of the knowledge about the effects of these best practices on the quality of palliative care is practice-based rather than evidence-based. At the moment, most evidence is available with regard to the Dutch version of the Liverpool Care Pathway (LCP) for the Dying Patient and regarding PaTz. Research has indicated that use of the Dutch version of the LCP leads to a decrease in the symptom burden for patients in the last days of life, a decrease in the grief burden for relatives and an improvement in the documentation of care [5-7]. Furthermore, a recent review showed that the Gold Standard Framework (the British equivalent of PaTz) improves processes in general practice, co-working and the quality of palliative care. Although the direct impact on patients and carers is unknown at present, the Gold Standard Framework has considerable potential to improve palliative primary care [8].

Although large-scale implementation of such best practices appears to be important for improving palliative care, implementation in general health care settings (e.g. general hospitals, general practices, residential elderly care and home care) is challenging, e.g. because professionals in general health care settings are often not specialized in palliative care and often provide care to a variety of patient categories. Moreover, hospital settings in particular are traditionally strongly focused on cure and life prolongation, which influences how palliative care needs are attended to [9].

### National quality improvement programme for palliative care

The Dutch National Quality Improvement Programme for Palliative Care was launched in 2012 with the aim of promoting the implementation of best practices in general health care settings. This four-year programme receives financial and practical support from ZonMw (The Netherlands Organisation for Health Research and Development) and was commissioned by the Dutch Ministry of Health. The programme’s key objectives are to promote that:

•Patients die at their preferred place.

•Patients and relatives feel they are in control regarding palliative care.

•Patients and relatives see palliative care as being coordinated.

•Patients and relatives feel care to be concordant with their needs, preferences and values.

•Patients and relatives receive care for their needs in the physical, psychosocial and spiritual domains.

This programme enables care organizations to improve their palliative care by implementing one or more of the available best practices. The best practices are pre-selected by an independent committee of experts, professionals and patient representatives, taking account of the available evidence, the usability and the transferability of the best practice to general health care settings. The committee assesses potential new best practices every year to include in the National Quality Improvement Program Palliative Care. The nine best practices that are currently pre-selected for implementation are listed in Additional file 1.

Every year during the programme period (2012–2016), there is a call for applications. Representatives of regional networks of palliative care providers are invited to choose a specific best practice from the pre-selected list and to submit a project proposal for an implementation trajectory. Each year, financial support is given by ZonMw for approximately 17 implementation trajectories. The grant applications are assessed by an independent quality working group. The criteria for granting this support include the requirement that the applicant must be a representative of the regional palliative care networks, the care organizations involved must reach a substantial number of patients with palliative care needs and the best practice chosen must be implemented within one year [10].

It is important to determine the effects of the National Quality Improvement Programme for Palliative Care, since a lot of professionals and financial resources are involved and ultimately patients and relatives must benefit from this great effort. Other large-scale improvement programmes have already been implemented and evaluated in other domains, e.g. regarding safety in health care and social care [11-15]. However, so far such large-scale programmes are a new feature within palliative care. Earlier evaluations in other health care domains not only focused on the effectiveness of the programmes but also described the implementation processes in order to enable an understanding of how the programmes take shape in practice, as well as of barriers and facilitators. Such a process evaluation can be referred to as opening the ‘black box’ of interventions [16], which is important in increasing the likelihood that interventions will continue to be used in practice after the research has finished. In palliative care too, it is important to bridge the gap between research and practice [17,18] and to maximize the likelihood of the long-term adoption of quality improvement projects in practice [19]. Therefore, it is important to describe both the effects and the process of this large-scale implementation of palliative care best practices.

### Objectives

This paper presents the study protocol of the evaluation study. The primary objective of this study is:

•To gain insight into the effects of the National Quality Improvement Programme for Palliative Care as a whole on the quality of palliative care at a national level.

Its secondary objectives are:

•To gain insight into the effects of the separate implementation trajectories of best practices on the quality of palliative care within the participating regional palliative care networks or organizations.

•To elucidate the measured effects by describing the implementation process and the barriers and facilitators within the separate implementation trajectories.

The specific research questions being addressed in the evaluation study are as follows:

1. What are the effects of the National Quality Improvement Programme for Palliative Care as a whole on the quality of palliative care? More specifically, what are the programme’s effects on:

a. The percentage of patients who die in their preferred place?

b. The extent to which patients and relatives feel in control regarding palliative care?

c. The extent to which patients and relatives experience well-coordinated palliative care?

d. The extent to which patients and relatives feel that the palliative care is concordant with their preferences and values and meets their needs in the physical, psychosocial and spiritual domains?

2. What are the effects of the separate implementation trajectories on the quality of palliative care at the level of the regional palliative care networks or care organizations involved? (with equivalent subquestions to questions 1a to 1d)

3. How and to what extent are the best practices implemented? More specifically:

a. Does the implementation of the best practices take place as planned?

b. What barriers and facilitators are there for the implementation of the best practices and what conditions have been created to ensure the best practices are maintained?

c. Are there any other factors or developments – inside or outside the participating organizations – that might have contributed to the measured effects of the programme as a whole or within the separate implementation trajectories?

## Methods

### Evaluation study design

The National Quality Improvement Programme can be considered as a complex intervention involving various implementation trajectories of various best practices within a continuously changing, uncontrolled environment. Therefore we opted for a quantitative effect evaluation with a pre-test post-test design (to answer research questions 1 and 2) in combination with a qualitative process evaluation with a post-test design (to answer research question 3). The combination of quantitative and qualitative methods is considered useful in gaining insight into the effects of the programme, as well as the implementation processes, barriers and facilitators for the implementation and internal or external factors that may influence the outcomes.

### Study population

All implementation trajectories receiving a grant in the National Quality Improvement Programme will participate in the evaluation study. Within the participating organizations, data will be collected from patients and bereaved relatives (see Figure 1). In implementation trajectories with more than five participating organizations, a purposive sample will be selected of care organizations with the highest number of patients meeting the inclusion criteria and representing all the different settings involved in the specific implementation trajectory.

